### Power calculations—first primary endpoint

It is estimated that 1600 test-negative controls and 400 dengue-positive cases will be needed to detect a 50% reduction in dengue incidence with 80% power. Sample size requirements will be re-estimated using observed data after attaining 50% of the target data collection.

We follow [44, 47, 54] to estimate the sample size for the proposed study design. We used the comparison of exposure odds among test-positive cases vs. test-negative controls for data aggregated across all clusters, with the null hypothesis that the odds of residence in a treatment cluster is the same among test-positive cases as test-negative controls [44, 47, 54]. This provides an unbiased estimate of the relative risk between groups as demonstrated previously [44, 47, 54].

We performed simulations (*n* = 1000) to estimate the power to detect a 50% intervention effect, assuming eight clusters per arm, and using available historical dengue testing data in the 15 study clusters. We randomly allocated eight clusters to receive the intervention; this random allocation was repeated 10,000 times, and allocations were only kept when constrained randomization criterion were met (*n* = 3151 possible balanced allocations). In each iteration of the simulation, we randomly selected one distinct intervention allocation and a 2-year time frame from the historical dengue testing data and simulated a 50% intervention effect in the intervention arm in the latter 12 months. The simulated data was analyzed using logistic regression to assess the significance of intervention effect. These were repeated for various dengue test sample sizes. We computed the proportion of significant results obtained in each scenario. This provided an estimate for the power of our study and the sample size required to obtain the respective power [44].

### Power calculations—second primary endpoint

Intervention efficacy in the second primary endpoint from the difference-in-differences strategy as described below, laboratory-confirmed dengue case counts normalized by cluster population size (incidence rate), which is aggregated at the cluster level and measured across months and across clusters. We followed [55] to estimate the required post-intervention duration required to detect a 50% reduction in dengue incidence rates with 80% power.

The power calculation was conducted by performing simulations (*n* = 1000) to estimate the power to detect a 50% intervention effect, assuming eight and seven clusters in the intervention and non-intervention arm respectively, and using historical dengue incidence rate data (2015–2021) in the 15 study clusters. These clusters were constrained randomized to obtain balanced intervention/non-intervention arms as delineated in the preceding section. In each iteration of the simulation, we randomly selected one distinct intervention allocation and 0.5, 1, 1.5, 2, 2.5, and 3 year time frames post-intervention, with pre-intervention period fixed at 4 years and simulated a 50% intervention effect in the intervention arm in the following intervention. The simulated data was analyzed using the difference-in-differences specification (see below) to assess the significance of intervention effect. We then computed the proportion of significant results obtained in each scenario. This provided an estimate for the power of our study and the measurement duration required to obtain the respective power.

We estimate that at least 31 months would be required post-intervention to detect a 50% reduction in dengue incidence rates at 80% power.

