### *Wolbachia* deployment strategy

Low-dose (~40 Gy or lower) X-ray-irradiated male *w*AlbB-infected *Ae. aegypti* (male *Wolbachia-Aedes*) will be released in designated public locations in high-rise housing estates in the intervention clusters [24]. Releases may commence across all intervention clusters simultaneously or, if operationally more feasible, be staggered between three lots across two months apart. Releases will be conducted twice a week, during periods of highest *Ae. aegypti* activity (weekdays between 0630–1100 h and 1300–1800 h) [24]. To facilitate even distribution of mosquitoes, releases will be conducted in equally spaced release locations per apartment block, on the ground, middle (levels 5–6) and high floors (levels 10–11). Based on previous studies [24], we expect to release 1–6 male mosquitoes per resident, with the release numbers adaptively guided by the Gravitrap index (see below) at each location each release week. Mosquito monitoring, as described in the following section, will continue throughout the study period. Male *Wolbachia-Aedes* will also be released twice a week on the ground floors of high- and low- rise housing estates within the designated buffer areas [50]. Where releases in buffer areas cannot be performed (e.g., schools), releases will be conducted at the boundary between such areas and the intervention sites. This is to counteract immigration of wild-type *Ae. aegypti* females from contiguous non-release areas.

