### Expected study duration

Deployment of male *Wolbachia*-*Aedes* and data collection from diagnostic laboratories is expected to commence in June 2022 (see Table 1). Data collection will continue for least 24 months or longer if needed to reach the minimum sample size required for intention-to-treat analysis. To account for year-to-year variability in dengue cases, data collection will continue for at least 24 months even if the estimated minimum sample size is attained sooner.

**Table 1 Tab1:** Trial timeline

Key activities	Period
Randomization	February 2022
Engage healthcare institutions for data collection [GPs, hospitals, polyclinics]	March 2022–June 2022
Phase 1 sentiment survey	March 2022–June 2022
Community engagement	June 2022 onwards
Start of RCT (releases at 8 intervention sites)	July 2022
Phase 2 sentiment survey	September 2022–December 2022
Phase 3 sentiment survey	December 2022–March 2023
End of RCT	September 2024
Final analysis	September 2024–November 2024
Publication of results	December 2024

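### The second primary endpoint is said to need at least 31 post-intervention months for 80% power, but the stated schedule gives 26 to 28 and no rule ties follow-up to the 31

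*Protocol article*

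**What the plan says.** The section on power for the second primary endpoint sets out its target: "We followed [55] to estimate the required post-intervention duration required to detect a 50% reduction in dengue incidence rates with 80% power". The simulation is described as "assuming eight and seven clusters in the intervention and non-intervention arm respectively" and as "using historical dengue incidence rate data (2015–2021) in the 15 study clusters". Post-intervention periods of 0.5 to 3 years in half-year steps were tried, with four pre-intervention years. The result is: "We estimate that at least 31 months would be required post-intervention to detect a 50% reduction in dengue incidence rates at 80% power".

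The section on expected study duration sets a floor: "data collection will continue for at least 24 months even if the estimated minimum sample size is attained sooner". It also allows a longer period if that is needed to reach a minimum sample size for the intention-to-treat analysis. Table 1 in that section puts the start of releases in July 2022, the end of the trial in September 2024, final analysis in "September 2024–November 2024" and publication in December 2024. The text above the table gives June 2022 as the start of deployment and data collection.

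The only minimum sample size in the protocol is the first endpoint's 400 cases plus 1,600 test-negative controls. The governance and interim-analysis sections count progress in the same unit: 500, 1,000 and 1,500 dengue tests.

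The deployment section adds that releases may start everywhere at once or, if that is easier operationally, "be staggered between three lots across two months apart".

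**The concern.** The second endpoint's information requirement is expressed in elapsed months. The schedule that is meant to supply those months stops short of it. The only clause that could lengthen the schedule appears to respond to a different quantity, the number of dengue tests. If 2,000 tests arrive early, stopping at 24 months complies fully with the duration section, yet falls seven months below what the power section requires.

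This is one of two primary endpoints. The Discussion says the difference-in-differences analysis was included to strengthen conclusions, given the limits of the test-negative design with few, small clusters. A reader of the results would take its power to be 80%, and the planned readout would not support that figure.

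**Working it through.** **1. The plan's own figure.** The 31 months comes from a simulation on 2015–2021 cluster incidence data. The article does not show those data, their variances or the final significance level, so the figure cannot be reproduced. It is taken as given. Post-intervention is read as time since releases began, which is how the power section uses it alongside the pre-intervention period.

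**2. Months supplied by the schedule.**
- July 2022 to September 2024: 2 × 12 + 2 = 26 months, or 27 counting both end months.
- June 2022 to September 2024: 2 × 12 + 3 = 27 months, or 28 counting both end months.
- Shortfall against 31: 3 to 5 months on the schedule, and 31 − 24 = 7 months at the floor.

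**3. When 31 full months would end.** From June 2022, at the end of December 2024. From July 2022, at the end of January 2025. Even the most generous count, June 2022 to November 2024 inclusive (the last month of the final-analysis window), gives 30 months.

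**4. Illustrative loss of power.** Assumptions: exactly 80% power at 31 months, two-sided alpha 0.05, and a normal approximation. With d = 1.960 + 0.842 = 2.802,

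power(m) = Φ( d × √(V(31)/V(m)) − 1.960 )

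where V(m) is the variance of the estimate with m post-intervention months. Model A takes V proportional to 1/m. Model B takes V proportional to 1/48 + 1/m, which allows for the four-year pre-period.

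Worked example, m = 26:
- Model A: 2.802 × √(26/31) − 1.960 = 0.606, and Φ = 0.728.
- Model B: V(31) = 0.02083 + 0.03226 = 0.05309 and V(26) = 0.02083 + 0.03846 = 0.05929. Then 2.802 × √(0.05309/0.05929) − 1.960 = 0.691, and Φ = 0.755.

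| Post-months | Model A | Model B | Model B with AR(1) monthly errors, correlation 0.5 to 0.9 |
|---|---|---|---|
| 24 (floor) | 0.693 | 0.733 | 0.737 to 0.763 |
| 26 | 0.728 | 0.755 | 0.758 to 0.775 |
| 27 | 0.744 | 0.765 | 0.767 to 0.780 |
| 28 | 0.759 | 0.775 | 0.776 to 0.785 |
| 31 (anchor) | 0.800 | 0.800 | 0.800 |

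**5. Staggered releases.** Three lots two months apart would start the last lot four months after the first, leaving it 22 to 24 months on the Table 1 schedule. This reduces the pooled information further. By how much depends on how the eight clusters are split into lots, which is not stated.

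**The case against.** Five points can be made for the plan.

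- **The duration is a floor, under a heading that calls it expected.** This stands in part. A reader might infer that 24 months is the only rule, and that is not so. The protocol applies intention-to-treat to both primary endpoints, so the extension clause could have been meant to cover the second as well. The text does not say so, and wherever a minimum is quantified it is a count of dengue tests. What can be said is that nothing expressly ties follow-up to 31 months.
- **The loss is small.** This stands as to size. The simulation used 1,000 replicates, so an estimate near 80% has a standard error of √(0.8 × 0.2/1000) = 0.0126, roughly ±2.5 percentage points at 95%. The top of the table's range at 28 months lies within that margin. The error runs both ways, however, and does not remove a stated requirement of 31 months.
- **A 50% effect is conservative, since earlier field trials reported an 88% reduction.** A larger true effect would have more power. But the Discussion chose 50% in order to absorb dilution from human movement, so the same margin cannot also pay for missing months.
- **Smooth scaling by months is doubtful for an epidemic disease.** This stands. Information follows outbreaks as well as the calendar, so the powers above are illustrations. The mismatch between 31 and 26 to 28 does not depend on them.
- **Staggering is optional, and Table 1 shows a single start.** This stands, so staggering is an additional risk and not part of the main count. It would also be wrong to quote a power for the last lot alone, because power belongs to the pooled comparison of eight against seven clusters.

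**Conclusion.** The point holds as an inconsistency between two sections. The second primary endpoint requires "at least 31 months would be required post-intervention", the timetable supplies 26 to 28, and no clause expressly links its follow-up to the requirement. The 80% power stated for that endpoint is therefore not a property of the stated schedule. The calendar finding rests only on the protocol's own dates.

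The size is moderate: about 73% to 78% power on the Table 1 schedule and about 69% to 73% at the 24-month floor, up to about 76% at the floor under strong autocorrelation. These values assume exactly 80% at 31 months, two-sided alpha 0.05 and the variance models shown.

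Two stronger conclusions are tempting and not supported. A reader might infer that a null result would be uninterpretable, but a loss of a few points of power at a 50% effect does not go that far. A reader might also infer that the 31-month figure is itself wrong. It is not one of the simulated durations, but it lies between two of them (30 and 36 months), so interpolation is a natural reading. If windows were contiguous, four pre-intervention years within 2015–2021 would put the whole of 2020, the record outbreak year, into every post-period of two years or more. The article does not say how windows were drawn. Both remarks are secondary and show no error in the text.

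**What to change.** Reconcile the two sections in one of two ways.

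- **Restate the power.** Re-run the existing simulation at the planned post-intervention duration and at the 24-month floor, with a staggered start if one was used. Report the resulting power for the second endpoint beside the 31-month figure. This costs one re-run of existing code and a sentence or two, and the end date need not move.
- **Tie the analysis to the requirement.** State that the second endpoint is analysed once its 31-month requirement is met, say from which date the months are counted (particularly if releases are staggered), and correct Table 1. The analysis cut-off would move by 3 to 5 months, to the end of December 2024 or January 2025, with the extra surveillance and a later publication date. Whether releases continue over those months is for the trial team.

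Either way, say which endpoint's minimum triggers the extension clause, and give one start date where the text now has June 2022 and Table 1 has July 2022.

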### Pre-post trial attitudes, acceptance, and knowledge survey on *Wolbachia-Aedes* interventions and other vector control practices

To assess efficacy of the various engagement strategies employed, an independent consultancy firm will be engaged to conduct door-to-door household perception surveys. These surveys will be used to measure (1) the effectiveness of different community engagement strategies and (2) each strategy’s efficacy in shaping community attitudes, perception, and knowledge pre- and post-intervention. Surveyors will be trained before data collection to ensure their understanding of the objectives, methodology, expectations, and questionnaires.

The surveys will be conducted in three waves, in households equally selected from the intervention and non-intervention clusters. The first survey will commence three months before and up until the beginning of *Wolbachia-Aedes* deployments. The second and third surveys will begin 3 months and 1 year following the commencement of *Wolbachia-Aedes* deployments respectively. Each survey wave will be split into three arms, (i) non-intervention clusters with no community engagement, (ii) intervention clusters with standard community engagement practices, and (iii) intervention clusters with alternate community engagement strategies. Households will be selected via stratified systematic sampling. Households will be stratified according to ethnic group denomination and minority socio-demographic factors and systemically sampled. Minority groups will be accounted for in higher proportions to reflect adequate representation of these groups. To accurately reflect the general sentiments of the working and non-working populations, surveys will be administered during the evenings of the working days and weekends. The sampled list of households across the different timepoints will be mutually exclusive to prevent contamination of questions across waves. Survey questionnaires used will be tailored to collect specific information across various timepoints and study arms. For each survey session, the surveyor will approach one respondent from each household to interview, after obtaining informed consent to participate. In the event of (i) resident refuses to participate and (ii) resident is not home, the surveyor will note down these households and arrange for a second visit, before approaching the next household on the list. In the event of a language barrier, surveyors will note the language requirements of the household and a second visit with a surveyor equipped with the necessary language skills will return to the household to conduct the survey. A maximum of one revisit to the same household will be attempted to accurately capture ground sentiments, while remaining prudent with resources.

The National Environment Agency’s (NEA) public feedback portal will also be used as an additional data source, to collect residents’ feedback submissions related to *Wolbachia-Aedes* deployment in all clusters. Submissions will be classified as positive or negative and tracked through the duration of the study to supplement understanding of residents’ attitudes, knowledge, and perceptions of the intervention.

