### Statistical analysis: secondary endpoint—impact of male *Wolbachia-Aedes* deployments on community attitudes/knowledge and acceptance

Using prospectively collected household survey data as described in preceding sections, we will test for differences in engagement and awareness across engagement arms in male *Wolbachia-Aedes* deployment clusters, across 3 sentiment surveys, after which differences and changes in residents’ knowledge attitudes and perceptions on male *Wolbachia-Aedes* deployment and vector control practices will be evaluated across intervention and engagement arms. Responses from all survey waves across intervention/non-intervention sites will first be hypothesis tested for differences in the captured socio-demographic characteristics. If there are between-wave differences in socio-demographic characteristics, propensity score matching will be conducted and/or synthetic weights assigned to each observation to mirror the national level socio-demographic composition. To examine the impact of the trial on community endpoints, logistic/multinomial regressions with site- and trial-specific fixed effects will be used, with socio-demographic controls added. An interaction term between site and trial indicator variables will be added to test overall outcome differences over time between intervention and non-intervention clusters and across engagement arms. Additionally, comparisons across engagement arms will be conducted to determine efficacies of engagement strategies. These analyses will then yield coefficients which allow computation of the odds and marginal odds ratios for each corresponding factor on the community attitude/knowledge/acceptance outcome measure referenced from baseline. Lastly, differences in number of positive and negative feedback submissions through NEA’s public feedback portal will be compared across intervention and non-intervention clusters and across the various engagement arms.

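### The baseline attitude survey is closed by the start of releases, not of community engagement, so some intervention-cluster baseline interviews may follow the engagement that the survey evaluates

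*Protocol article*

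**What the plan says.** All of this is in the protocol article.

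- **Purpose of the survey.** The survey section has two aims: to measure how well different engagement strategies work, and how they shape attitudes, perception and knowledge before and after the intervention. Engagement is therefore an exposure under evaluation.
- **Timing of the baseline wave.** The same section says "The first survey will commence three months before and up until the beginning of" deployments. The closing event is the first release.
- **Survey arms.** Arm (i) is "non-intervention clusters with no community engagement". Arms (ii) and (iii) are intervention clusters with standard or alternate engagement.
- **Calendar (Expected study duration, Table 1).** The rows read "Phase 1 sentiment survey March 2022–June 2022", "Community engagement June 2022 onwards" and "Start of RCT (releases at 8 intervention sites) July 2022". The text above the table differs on releases: deployment and "data collection from diagnostic laboratories is expected to commence in June 2022".
- **Analysis.** The section on community attitudes fits logistic or multinomial regressions with a site-by-trial interaction and compares engagement arms. It reports odds ratios for the "outcome measure referenced from baseline".

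**The concern.** A baseline should precede the exposure whose effect it anchors. Here there are two exposures, engagement and releases, and in Table 1 engagement comes first. Closing the baseline wave at the later event allows interviews taken after the earlier one to count as baseline.

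Any such overlap would be one-sided. Trial engagement is described for arms (ii) and (iii) and excluded from arm (i). A baseline in the intervention clusters that already carries some of the engagement effect would shrink both the within-arm change and the interaction with the non-intervention clusters.

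The survey section does guard against another form of contamination, since no household is sampled in more than one wave. It has no corresponding rule for baseline interviews held after engagement has begun.

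**Working it through.** The article gives no sample size, effect size or power for the survey, so there is no figure to reproduce. The check is calendar arithmetic followed by a simple attenuation formula.

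**Inputs**
- Phase 1 window: March to June 2022 (Table 1), at most 1 March to 30 June = 122 days.
- Start of community engagement: June 2022, no day given (Table 1).
- Start of releases: July 2022 (Table 1) or June 2022 (text of Expected study duration).
- Assumed: interviews spread evenly over the window. The article does not say.

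**Step 1: share f of baseline interviews that could follow engagement**

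f = days from engagement start to 30 June / 122

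| Engagement starts | Overlap (days) | f |
|---|---|---|
| 1 June | 30 | 30/122 = 24.6% |
| 15 June | 16 | 16/122 = 13.1% |
| 30 June | 1 | 1/122 = 0.8% |

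If instead the text's June release date is used, with releases on 1 June and the wave closing then, the three-month window is 1 March to 31 May (92 days). Engagement cannot start before 1 June, so the overlap is 0 days and f = 0.

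f therefore runs from 0 to about 0.25.

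**Step 2: effect on the contrast**

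Let D be the true change in the intervention clusters, over and above that in the non-intervention clusters. Let r be the share of D already present in respondents interviewed after engagement began. On an additive scale the intervention-arm baseline is raised by f*r*D, and arm (i) is unchanged, so:

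estimated contrast = D - f*r*D = D(1 - f*r)

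| r | f = 0 | f = 0.125 | f = 0.25 |
|---|---|---|---|
| 0.25 | 1.00 | 0.97 | 0.94 |
| 0.5 | 1.00 | 0.94 | 0.875 |
| 1 | 1.00 | 0.875 | 0.75 |

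As an illustration, an assumed true change of +20 percentage points would read as 20 x 0.75 = +15 at the lower limit, and as 20 x 0.875 = +17.5 with f = 0.25 and r = 0.5. The planned models work on the odds scale, so these factors are approximate there. Neither f nor r can be fixed from the article.

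**The case against.** **Overlap is not demonstrated.** A reader might infer that part of the baseline was in fact taken after engagement and that the contrast is attenuated. The documents do not support that. Table 1 gives a shared boundary month and no days. A June release start also fits the survey dates well: March is three months before June, and September, when Phase 2 starts, is three months after. On that reading the wave could close in early June with little or no overlap. This objection stands, and the finding is confined to what may happen. It does not remove the point, because Table 1 itself ends Phase 1 in June and puts releases in July, and no rule prevents overlap.

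**A larger share can be computed.** Three months before a 1 July release is 1 April to 30 June, and 30/91 = 33.0%. That window contradicts the March start in Table 1, so 33% is not used as the limit.

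**Engagement is not confined to one arm.** Study setting keeps routine vector control and publicity going in both arms, and the Discussion keeps community engagement going as usual. The engagement described under randomization is aimed at political and grassroots leaders, so it may not reach households at once. Both observations stand, and the second argues for a small r. Routine activity common to both arms does not cancel a difference created by trial engagement, which the survey section excludes from arm (i).

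**Fast-acting strategies would look weakest.** This is tempting but does not follow. A strategy worth +20 points would still read +15 at the lower limit. A slower one with no June effect would outrank it only if its true effect exceeded +15.

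**The direction is assumed.** For r between 0 and 1 the contrast moves toward no effect. If early engagement first raised concern, acceptance could be biased the other way.

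**The anchor suits the endpoint.** The analysis section is headed by deployments, and comparisons between engagement arms do not rest only on the first wave. This is fair for the deployment question. It does not cover the engagement aim or the estimates referenced to baseline.

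**Conclusion.** The point holds as a risk that the stated rule leaves open. The baseline wave is closed by releases although the survey also evaluates engagement, and Table 1 puts the end of Phase 1 and the start of engagement in the same month, before releases. Baseline interviews in arms (ii) and (iii) may therefore follow trial engagement while those in arm (i) do not, and the pre-post and interaction estimates may be attenuated.

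Under even fieldwork and an additive effect, the loss ranges from none to about a quarter of the true contrast. The upper end needs engagement from 1 June, Phase 1 running to 30 June, and a full effect at once. A later start or a slower effect brings it well below that.

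One secondary endpoint is affected. Neither primary dengue endpoint depends on the survey. The correction is worth making because it is cheap and, if interview and engagement dates were kept, still possible after fieldwork.

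**What to change.** 1. Reconcile the June and July 2022 dates for first release within Expected study duration, and state when Phase 1 interviewing closed.
2. Define baseline in each intervention cluster as the Phase 1 interviews completed before the first trial engagement activity in that cluster. State which activities count, so that contact with leaders is distinguished from activity that reaches households.
3. Non-intervention clusters have no engagement date, so apply one stated calendar cut to them, for example the earliest engagement date in any intervention cluster. Adjusting for interview date is an alternative.
4. Report the results with and without post-engagement Phase 1 interviews. If there are none, one sentence saying so settles the matter.

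**Cost.** A few sentences in the survey and analysis sections, and recoding by dates the sponsor should hold. Up to about a quarter of baseline interviews could be excluded, with some loss of precision. Late interviews may include more households reached only on a second visit (not at home, initial refusal, language need), so the cut could under-represent them. Reporting both versions shows whether that matters.

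### The between-arm difference in the number of deployment-related portal submissions mixes occasion to comment, engagement and opinion, so it cannot be read as a difference in acceptance

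*Protocol article*

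**What the plan says.** The portal is described at the end of the protocol's section on the attitudes, acceptance and knowledge survey. The data are restricted by topic, to what residents submit about the Wolbachia-Aedes "deployment in all clusters. Submissions will be classified as positive or negative and tracked through the duration of the study". Each item thus carries one of two labels, and the stated purpose is "to supplement understanding of residents’ attitudes, knowledge, and perceptions of the intervention".

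The analysis is in the statistical section for the secondary endpoint on community attitudes/knowledge and acceptance. Its last sentence names the quantity as "differences in number of positive and negative feedback submissions through NEA’s public feedback portal". The groups set against each other are the two trial arms and, separately, the engagement arms. The measure is therefore a number, and no denominator is given.

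Two other sections bear on this. Under the Wolbachia deployment strategy, the mosquitoes "will be released in designated public locations in high-rise housing estates in the intervention clusters", with further releases in the buffer areas around them. The survey section defines the comparison arm as "non-intervention clusters with no community engagement", while the randomization section plans extensive community engagement directed at the eight intervention clusters.

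**The concern.** The topic filter selects on something that the allocation creates. A resident of a release cluster sees releases twice a week and lives where the trial is explained and promoted. A resident of a non-intervention cluster has neither nearby. The number of deployment-related submissions will therefore depend on arm even if residents of both arms hold the same view of the intervention.

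The result is placed under an endpoint about attitudes and acceptance. An excess of negative submissions in the intervention arm could be read as lower acceptance, and an excess of positive ones as higher acceptance. Both excesses could arise together from a difference in how often people submit.

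**Working it through.** The plan gives no rate, sample size or expected volume for the portal, so there is no figure of its own to reproduce. The check is whether the stated measure can separate opinion from occasion to comment.

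**Inputs from the protocol**
- 8 intervention and 7 non-intervention clusters (Study design).
- Only deployment-related submissions count (survey section).
- The measure is the number of positive and of negative submissions (secondary endpoint analysis).

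**Assumed inputs**
- Clusters of equal population.
- A mean of 2 submissions per non-intervention cluster.
- 60% of submissions negative in both arms, so no difference in opinion.
- Release-cluster residents submit *r* times as often, with *r* = 1, 2, 5 or 10.

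**Expected counts**

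Expected negative submissions in an arm = clusters × submissions per cluster × share negative.

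- Non-intervention: 7 × 2 × 0.6 = 8.4 negative and 7 × 2 × 0.4 = 5.6 positive.
- Intervention: 8 × 2*r* × 0.6 = 9.6*r* negative and 8 × 2*r* × 0.4 = 6.4*r* positive.
- Ratio: 9.6*r*/8.4 = 6.4*r*/5.6 = (8/7)*r* for both labels.

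| *r* (assumed) | Negative, intervention v non-intervention | Positive, intervention v non-intervention | Ratio of counts | Ratio per resident |
|---|---|---|---|---|
| 1 | 9.6 v 8.4 | 6.4 v 5.6 | 1.14 | 1 |
| 2 | 19.2 v 8.4 | 12.8 v 5.6 | 2.29 | 2 |
| 5 | 48.0 v 8.4 | 32.0 v 5.6 | 5.71 | 5 |
| 10 | 96.0 v 8.4 | 64.0 v 5.6 | 11.43 | 10 |

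The share negative and the mean of 2 cancel from the ratio. What remains is 8/7 from the allocation and *r* from the submission rates. A per-resident denominator removes the 8/7 and leaves *r*.

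**How often this would look like a finding**

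In 4,000 simulated trials per value of *r*, counts were Poisson and opinion was identical. Negative counts were compared by an exact binomial test with null share 8/15, so the allocation was already adjusted for. The test was significant at 5% in 3.6% of runs at *r* = 1, 38% at *r* = 2, 99.95% at *r* = 5 and 100% at *r* = 10. These percentages depend on the assumed volume of 2 per cluster; the ratios in the table do not.

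**Share instead of count**

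In the same runs, a Fisher exact test on the share negative rejected in 3.0% to 3.6% at every *r*. This holds because the simulation multiplies positive and negative submissions by the same factor. If releases multiplied negative submissions by 5 and positive ones by 2 (assumed), the share negative in release clusters would be 0.6 × 5 / (0.6 × 5 + 0.4 × 2) = 3.0/3.8 = 79%, against 60% elsewhere, again with no difference in underlying opinion. A share removes differences in overall volume, but not self-selection by opinion.

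**The case against.** **The portal is only a supplement.** The protocol calls it an additional source, gives its analysis one closing sentence, and attaches no model or hypothesis to it. The household surveys and their regressions carry the endpoint. This stands and sets the severity. It does not remove the problem, because the sentence sits under the acceptance endpoint and states both the measure and the contrast.

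**A condensed article leaves detail elsewhere.** This is true of denominators and tests. The point concerns what is stated (the topic filter, the count and the arms compared), not what is absent.

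**Some of the remedy is already planned.** This stands. Comparison across engagement arms and tracking through the study are in the text. Both engagement arms lie within intervention clusters, so the lack of releases does not affect that comparison.

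**Counts have a use.** They do, as a description of public reaction and workload where releases occur. They can be kept under that label.

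A reader might go further and infer that any between-arm difference reflects only the presence of releases, that the counts carry no information on opinion, or that an excess in the intervention arm is practically certain. The documents do not support this. Routine media engagement on vector control continues in both arms, field trials have run in Singapore since 2016, and submissions are to be collected from all clusters. Non-intervention residents can therefore comment, and opinion may contribute to a difference. No portal volume is given for either arm, so the size of any excess is unknown, and a large ratio in an illustration only returns the submission rates put into it.

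**Conclusion.** The point holds as a limit on interpretation. The planned between-arm count contrast cannot separate occasion to comment and engagement from opinion, so it should not serve as evidence on acceptance. With identical opinion and equal-sized clusters, the count ratio is (8/7) × *r* for positive and negative submissions alike. For *r* between 2 and 10 this is about 2.3 to 11.4, and per resident it is *r*. The values of *r* are assumptions; the direction *r* > 1 is a reasonable expectation from where releases and engagement take place, not a figure in the protocol.

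The point is minor. It affects one supplementary comparison within a secondary endpoint. The primary endpoints, sample size, interim rules and survey analysis are untouched.

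**What to change.** Change the last sentence of the analysis section for the attitudes/knowledge and acceptance endpoint as follows:

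1. Do not use the intervention versus non-intervention count contrast as evidence on acceptance. Drop it, or report it only as descriptive submission volume.
2. Keep the planned comparison across engagement arms within the intervention clusters and the tracking over time, but express both as the share of submissions that is positive, summarised by cluster.
3. State that portal submitters are self-selected, that engagement may change who submits, and that only eight clusters are available for the engagement-arm comparison.
4. Take the between-arm comparison of attitudes from the household survey already planned, which samples both arms.

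The cost is wording only; no new data are needed. The downside is that the portal then gives no intervention versus non-intervention comparison of acceptance, and the remaining comparisons rest on few clusters.
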